## Statistical methods

### Statistical methods for primary and secondary outcomes {20a}

The primary analysis will be by intention-to-treat (ITT), including all randomized patients who have undergone renal transplantation. A per-protocol analysis will also be performed with all patients. Demographic and clinical parameters will be described by mean and standard deviation or median and its confidence interval for continuous variables depending on the normal or non-normal distribution of the sample. Categorical variables will be described by absolute and relative frequencies. In addition, differences between groups will be calculated using Student’s *t*-test or Mann–Whitney *U* test depending on the sample distribution and the chi-square test. Time to incisional hernia onset will be described by Kaplan–Meier survival analysis and compared by log-rank test. The analysis will include stratification by the variable “obesity”. A *p*-value < 0.05 will be considered statistically significant. We performed our analyses with Stata v16.1 (StataCorp, TX, USA).

### Interim analyses {21b}

Given that these assumptions are based on the literature and may be modified, 2 interim analyses are proposed when 25 and 50 patients in each arm have been randomized and followed for 24 months. An independent committee constituted by the Clinical Biostatistics Unit will review the results in a blinded fashion and establish a recommendation for the principal investigator regarding the continuation of the study or modification of the sample size.

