### Plans for communicating important protocol amendments to relevant parties (e.g. trial participants, ethical committees) {25}

Principal Investigator (sponsor) will be responsible for communicating important protocol modifications including interruption or changes in recruitment of the study due to interim analysis results, to relevant parties: trial investigators, REC/IRBs and trial participants.

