
### Trial status

Protocol version 2.0. (02–18-2021).

Registered on 08 March 2021.

Recruitment is expected to start on 1 May 2021. Recruitment will be approximately completed in May 2023.

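### Both interim analyses wait for 24-month data, but recruitment is planned to last about 24 months, so neither look can change the planned recruitment

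*Protocol article*

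**What the plan says.** Interim analyses {21b} sets the trigger: "2 interim analyses are proposed when 25 and 50 patients in each arm have been randomized and followed for 24 months". The reason given is "Given that these assumptions are based on the literature and may be modified". A committee formed by the Clinical Biostatistics Unit is to review the results blinded and advise the principal investigator "regarding the continuation of the study or modification of the sample size".

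The section on communicating protocol amendments {25} makes the sponsor responsible for announcing important modifications, "including interruption or changes in recruitment of the study due to interim analysis results".

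Trial status gives the calendar: "Recruitment is expected to start on 1 May 2021. Recruitment will be approximately completed in May 2023".

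Three other places matter. Sample size {14} sets 76 patients per group. Participant timeline {13} schedules visits at 3, 6, 12 and 24 months. Section {11b} rules out any further change to the allocated closure once the abdominal wall has been closed.

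**The concern.** The looks are there because the design assumptions are uncertain, and the article itself shows how uncertain. The literature incidence is 1.6–18%, the sample size assumes 20% in controls, and the centre's own cohort showed 25% at 2 years. An early check could lead to a change while patients are still being enrolled. A check that needs 24 months of follow-up on 50 and then 100 patients cannot do this when enrolment itself lasts about 24 months.

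Two things are at stake. First, if the control rate is well below 20%, the shortfall in power is found only after enrolment has ended. Second, the intervention is given once, at closure. When either look takes place on the planned dates, every planned patient has already been operated on. Section {25} thus gives the interim results a function that the schedule does not allow.

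**Working it through.** **Inputs.** 25 and 50 per arm, so k = 50 and k = 100 patients in total, each followed for 24 months ({21b}). N = 2 × 76 = 152 ({14}). Recruitment length R of about 24 months (Trial status). The envelope is opened on the day of transplantation ({16c}), so randomisation and closure effectively coincide. Uniform accrual is an assumption.

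**The plan's own figure.** For 20% versus 5%, two-sided alpha 0.05, power 80%, no continuity correction, with pooled proportion 0.125:

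n = [1.960 × √(2 × 0.125 × 0.875) + 0.842 × √(0.20 × 0.80 + 0.05 × 0.95)]² / 0.15² = 75.1, rounded up to 76 per group. The stated size reproduces and is not in dispute.

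**Timing on the planned dates.** Accrual rate = 152 / 24 = 6.33 per month. Look time = k / rate + 24.

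| | k-th patient randomised | Look | After closure (month 24) |
|---|---|---|---|
| Look 1 (k = 50) | month 7.9 | month 31.9 (late December 2023) | 7.9 months |
| Look 2 (k = 100) | month 15.8 | month 39.8 (late August 2024) | 15.8 months |
| Last patient | month 24 | month 48 | 24 months |

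**Dependence on the accrual pattern.** Even the first patient reaches 24 months no earlier than 1 May 2023. If the 50th and 100th patients came in half the uniform time, the looks would be at months 27.9 and 31.9; in a quarter of the time, at months 26.0 and 27.9. If May 2023 is read as the last day of that month, look 1 could fall inside the window only if 50 patients were randomised in the first month, against an average of 6.33.

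**Dependence on the recruitment length.** A look precedes closure only if R × k/152 + 24 < R, that is R > 24 / (1 − k/152).
- Look 1: 24 / (1 − 50/152) = 35.8 months.
- Look 2: 24 / (1 − 100/152) = 70.2 months.

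With R = 30 months, the looks are still 3.9 and 13.7 months late. With R = 36, look 1 falls at month 35.8, with about 151 of 152 patients randomised, and look 2 is 11.7 months late.

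**What a late check could miss (illustration).** Assume a control rate of 10% and the same 75% relative reduction, so 10% versus 2.5%. Then z = [0.075 × √76 − 1.960 × √(2 × 0.0625 × 0.9375)] / √(0.10 × 0.90 + 0.025 × 0.975) = −0.05, and power is about 48% instead of 80%.

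**Timing with a 3-month trigger.** Look 1: 7.9 + 3 = 10.9 months, with 10.9 × 6.33 ≈ 69 randomised and 83 to come. Look 2: 15.8 + 3 = 18.8 months, with about 119 randomised and 33 to come.

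**The case against.** The strongest reply is that the recruitment end is only approximate and the looks only proposed, and that a late look still has uses. Part of this stands. On the planned dates follow-up runs to month 48, so both looks come before its end and could bear on whether to continue it.

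Four stronger readings are tempting, and the documents do not support them.

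- *The sample size cannot be changed at all.* It can be raised by reopening recruitment 8 or 16 months after closure. The article makes no provision for this, but does not exclude it.
- *The plan promises to limit patient exposure and fails.* The article names continuation, sample size and recruitment. Exposure is a reader's inference.
- *Patients are unprotected during enrolment.* The looks are justified by uncertain assumptions, not presented as the safety safeguard. Section {22} requires immediate reporting of adverse events to the sponsor, section {17b} allows unblinding when a severe wound complication requires mesh removal, and a data monitoring committee is named. A meeting schedule may sit in the full protocol.
- *At the centre's own volume both looks are bound to be late.* The 130 transplants in 2016 and 2017 give 130 / 24 = 5.42 per month and 152 / 5.42 = 28.1 months. That is a lower bound, reached only if all 130 were eligible and consented, and the article does not say that 130 was the full volume. Look 1 precedes closure if accrual falls below 152 / 35.8 = 4.25 per month, that is if fewer than 4.25 / 5.42 = 78% enrol. At 60%, as an illustration, accrual is 3.25 per month and recruitment takes 46.8 months; look 1 is at month 39.4 with about 128 randomised, and look 2, at month 54.8, is still late.

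None of this removes the conflict with the dates that the article states.

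**Conclusion.** The concern holds in this limited form. On the stated calendar both looks come after recruitment has closed, by about 8 and 16 months under uniform accrual. They cannot interrupt or change the planned recruitment, or reduce the number operated on. An increase in sample size would require reopening recruitment. An effect on remaining follow-up is still possible.

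The order of events within the planned window does not rest on uniform accrual; the exact months do. A moderate delay does not cure it: recruitment would have to exceed about 36 months for look 1 and about 70 for look 2.

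This is a should-fix point. The late timing alone does not bias the primary estimate, and the planned 76 per group is reproduced. What fails is the role that the article gives to the looks.

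**What to change.** Reconcile {21b}, {25} and Trial status by amendment.

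1. Trigger the two reviews when 25 and 50 patients per arm have completed an existing earlier visit. For the 3-month visit this is about months 11 and 19.
2. Use them for the wound-complication outcomes already listed under Secondary end-points: seroma, wound infection, pain and mesh removal. To respect the blinded review in {21b}, show the arms under codes. Give mesh removal so that it does not reveal the arms, for example as one total, since controls have no mesh.
3. Base any sample-size check at these times on the pooled hernia rate only.
4. Remove from {25} the implication that looks at 24-month data steer recruitment.

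The amendment uses existing visits and listed outcomes. The cost is in information. The centre's onset times had a median of 17.1 months and a lower quartile of 2.6. At look 1 the first 50 patients would have between 3 and 10.9 months of follow-up, about 7 on average. The pooled rate of 12.5% implies 50 × 0.125 = 6.25 hernias by 24 months. Linear interpolation between the quartiles puts about 32% of them before month 7, so roughly 2 hernias. The early reviews would therefore inform mainly safety, and test the 20% versus 5% assumption only weakly. A later existing visit gives more hernia data but leaves fewer patients still to be randomised.

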## Introduction

### Background and rationale {6a}

#### Background

Incisional hernia is a common complication after kidney transplantation with an incidence of 1.6–18.0% [1–4]. Several studies have identified multiple risk factors for the development of post-transplant incisional hernia that can be grouped into patient and donor factors, factors related to immunosuppression and factors related to the location and type of surgical incision [1–7]. In 2018, Simson et al. published a systematic review of the existing literature that highlights the limited scientific evidence that is mainly constituted by the review of case series. The risk factors identified were body mass index (BMI) > 30, age > 50 years, cadaveric donor transplantation and the need for reoperation [2]. The essential immunosuppressive therapy after transplantation has a negative impact on wound healing and leads to the formation of dysfunctional scar tissue. In the case of immunosuppressive medication, nucleotide synthesis inhibitors such as mycophenolate and mammalian target of rapamycin (m-TOR) inhibitors such as sirolimus have been associated with a higher incidence of incisional hernia [8].

Artificial mesh is commonly used in ventral incisional hernia repair as described in the literature, but there is yet no scientific paper on the use of prophylactic mesh placement at the time of transplantation. The main reason, therefore, is that immunosuppressive therapy and artificial mesh implantation seem to be contradictory due an increased risk of complications. Concerning non-transplant patients, a recently published meta-analysis by Borab et al. describes a reduction of the incidence of incisional hernia of up to 85% due to prophylactic mesh replacement in elective, midline laparotomy [9].

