### Sample size {14}

For the primary endpoint (incisional hernia at 24 months), assuming a proportion in the control group of 20%^1^ and a proportion of 5% in the intervention group (prophylactic mesh reinforcement placement), with an alpha level of 0.05 and power of 80%, the sample size per group was calculated at 76 patients.

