### Composition of the data monitoring committee, its role and reporting structure {21a}

Not applicable. There is no steering committee. The Clinical Biostatistics Unit will constitute the data management team and data monitoring committee that it is independent from the sponsor and free of competing interests.

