### Adverse event reporting and harms {22}

Adverse events will be immediately communicated to the trial sponsor (Principal Investigator) by the patient, investigators of the trial or other care providers. A trial’s phone and e-mail contact will be provided to all trial participants.

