Muysoms et al. in 2017 conducted the review of all published articles on the use of prophylactic mesh reinforcement (excluding studies on para-stomal hernia prevention) with no restrictions on the type of study or qualitative analysis [20]. All data on the degree of contamination and number of wound and/or mesh infections were extracted and analysed. The use of prophylactic mesh reinforcement to prevent incisional hernias had been published in the literature in 1,759 patients, with an overall wound infection rate of 12% and a mesh infection rate of 0.6%. The procedure, it was concluded, could be considered safe and effective in both clean and clean-contaminated surgery. Regarding the position of the prophylactic mesh, both supraaponeurotic and retromuscular positions have been used. Both seem equally safe and effective and probably the position of the mesh will depend on the preference of each surgeon. However, to identify in which group of at-risk patient’s prophylactic mesh should be recommended, the authors conclude that further studies are needed. In contrast, the existing literature on the prophylactic use of mesh for wall closure in the context of renal transplantation is very scarce [22–25]. Of the 3 articles identified, 2 of them refer to their use for the prevention or treatment of compartment syndrome in renal transplantation [22, 23]. Beasley et al. use a propylene mesh as a bridge between the posterior fascial planes with the aim of achieving enlargement of the closure and reduction of the pressure exerted on the graft; in this way, the graft was saved in 15 of the 17 cases used, the associated complications being minor in all cases with the occurrence of 5 cases of seroma and 1 lymphocele. In 2015, Wood et al. publish the use of prophylactic polypropylene mesh in the prophylaxis of compartment syndrome in renal transplantation. Of a total of 134 patients in whom mesh was implanted only 1.5% developed surgical wound infection, a result similar to that of the non-implanted population (1.3%). The mesh removal rate was 6% (8/134). Only the article by Michalski et al. referred to the use of mesh for prophylaxis of early surgical wound complications [22]. A reduction, although not significant, of surgical wound complications was identified in the group in which closure reinforced with Vycril™ (polyglactin 910) resorbable mesh was used. No association was identified between the use of prophylactic mesh and the occurrence of surgical wound infections, a potential complication feared by the use of mesh in the context of immunosuppression and transplantation.

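### Both scheduled committee reviews fall after the last planned mesh implant, and no earlier between-arm review of wound harm is stated

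*Protocol article*

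**What the plan says.** All references are to the protocol article.

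- **Interim analyses {21b}.** Two analyses are planned because the design assumptions come from the literature and may change. They take place when 25 and 50 patients per arm have been randomised and followed for 24 months. The committee "will review the results in a blinded fashion and establish a recommendation for the principal investigator regarding the continuation of the study or modification of" its planned size. The section does not define the blinding.
- **Composition of the data monitoring committee {21a}.** "The Clinical Biostatistics Unit will constitute the data management team and data monitoring committee". The unit is described as independent of the sponsor. The entry opens as not applicable and gives no safety schedule or remit.
- **Adverse event reporting and harms {22}.** The reporting route is given in one sentence: "Adverse events will be immediately communicated to the trial sponsor (Principal Investigator) by the patient, investigators of the trial or other care providers". No onward step to the committee is given.
- **Procedure for unblinding {17b}.** The principal investigator alone may unblind a patient whose severe wound complication requires mesh removal.
- **Background {6a}.** Prophylactic mesh has not been studied at transplantation, mainly because "immunosuppressive therapy and artificial mesh implantation seem to be contradictory due an increased risk of complications". The Discussion repeats the infection concern, and Trial design {8} aims for fewer hernias at minimal risk of complications.
- **Sample size {14} and Trial status.** "the sample size per group was calculated at 76 patients". Recruitment runs from 1 May 2021 to about May 2023.
- **Participant timeline {13}.** Visits are at 3, 6, 12 and 24 months.

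**The concern.** Wound infection, seroma and mesh removal are the harms that the protocol lists as secondary safety outcomes, and early wound events can be counted at the first scheduled visit. The decision they bear on, whether to keep implanting mesh in immunosuppressed patients, is open only during recruitment. The committee's only stated reviews wait for the 24-month hernia time point. If recruitment itself takes about 24 months, a recommendation on continuing the study can no longer spare anyone a mesh.

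Adverse events meanwhile go to the principal investigator, who is also the sponsor and enrols patients. That channel carries single cases, not rates by arm. An early excess of wound complications in the mesh arm could therefore go uncompared until all 76 intervention patients had been exposed.

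**Working it through.** **The plan's own figure.** Control 20%, mesh 5%, alpha 0.05 (taken as two-sided), power 80%; mean proportion 0.125.

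n = [1.960·√(2·0.125·0.875) + 0.842·√(0.20·0.80 + 0.05·0.95)]² / 0.15² = 75.1, rounded up to 76 per group. The stated size reproduces, giving 152 patients, 76 with mesh.

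**Timing of the stated reviews.** Randomisation takes place on the day of transplantation (Implementation {16c}), so enrolment and implantation coincide. Assume uniform 1:1 accrual over 24 months: 152/24 = 6.33 patients per month. The reviews need 50 and 100 patients in total.

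| Review | Last required patient randomised | +24 months | After recruitment ends (month 24) |
|---|---|---|---|
| 25 per arm | 50/6.33 = month 7.9 | month 31.9 | about 8 months |
| 50 per arm | 100/6.33 = month 15.8 | month 39.8 | about 16 months |

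The order does not depend on uniform accrual. Each review comes 24 months after its last required patient, who is randomised some time after month 0, so it falls after month 24 whatever the accrual pattern.

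**Sensitivity to recruitment duration (uniform accrual).**

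| Recruitment | First review | Second review |
|---|---|---|
| 18 months | month 29.9 | month 35.8 |
| 24 months | month 31.9 | month 39.8 |
| 30 months | month 33.9 | month 43.7 |
| 36 months | month 35.8 (about 151 of 152 enrolled) | month 47.7 |

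The first review precedes the end of recruitment only if recruitment exceeds 24/(1 − 50/152) = 35.8 months, and the second only if it exceeds 24/(1 − 100/152) = 70.2 months.

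**The same patients at the existing 3-month visit (24-month recruitment).**

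- 25 per arm: month 7.9 + 3 = 10.9. Enrolled 6.33 × 10.9 = 69, of whom 34.5 have mesh. Implants still to come: 76 − 34.5 = 41.5.
- 50 per arm: month 15.8 + 3 = 18.8. Enrolled 119, of whom 59.5 have mesh. Implants still to come: 16.5.

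**What such reviews can see.** As an illustration only, take wound infection of 12% against 24%. The 12% is the rate the Discussion gives for prophylactic mesh in general; the 24% is an assumed doubling. Fisher's exact test at two-sided 0.05 finds this excess with probability about 11% at 25 per arm and 26% at 50 per arm. The tables can show large differences only.

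**The case against.** **A journal article may leave this to a charter or the full protocol.** Safety schedules and onward reporting often sit there, and mere silence would be no finding. That stands as a caution. But the article does answer the interim, committee and harms items, and it fixes both the 24-month condition and the recruitment window. The timing conflict follows from those statements.

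**Safeguards exist.** A reader might infer that there is no committee, or that nothing at all could prompt a reaction to harm. The text does not support that. A data monitoring committee is named, adverse events must be reported at once, and the principal investigator can unblind a patient who needs mesh removal. Nor does the interim section exclude wound outcomes: it speaks of results in general. These safeguards work patient by patient, however, and a general reading of the results does not bring the reviews forward.

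**Blinding.** A reader might infer that a blinded review must hide a mesh-arm excess. That goes too far. The article does not say whether blinded means pooled or masked by arm code, and arm-coded tables would show an imbalance. Even pooled mesh removals are, crossovers aside, mesh-arm events.

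**Evidence of harm.** A reader might take the 6% mesh removal rate (8/134) in the Discussion as the rate to expect here. It comes from mesh used against compartment syndrome in renal transplantation. The same paragraph reports wound infection of 1.5% with mesh against 1.3% without, and a 0.6% mesh infection rate in the wider literature. The point rests on the acknowledged uncertainty, not on a demonstrated excess.

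**Conclusion.** The point holds as one about timing and remit. On the planned dates, both stated committee reviews come after all 76 mesh implants, by about 8 and 16 months under uniform accrual. Unless recruitment runs beyond about 36 months, the first review comes too late to affect any implant. No earlier between-arm review of wound harm is stated, and adverse events have no stated route to the committee.

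The conclusion assumes the planned recruitment window and that no unseen document adds earlier safety reviews. The exact months assume uniform 1:1 accrual. It does not depend on what blinded means, nor on any particular complication rate. The change is worth making because it is cheap and the protocol itself names the risk.

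**What to change.** 1. Amend Interim analyses {21b} and the committee section {21a}. When 25 and then 50 patients per arm reach the existing 3-month visit, the existing committee also reviews surgical wound infection and seroma by masked arm code, and the total number of mesh removals. Hernia data are not tabulated, so no efficacy alpha is spent.
2. Amend Adverse event reporting {22} so that adverse events go to the committee as well as to the principal investigator.
3. Have the sponsor and committee settle and record beforehand any criterion for advising a pause in enrolment. No threshold is proposed here.

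**Cost.** One amendment and two short tables of outcomes the trial already collects, with no new committee, visit or patient. There are two real downsides. Mesh removals can reveal which code is the mesh arm, and the Clinical Biostatistics Unit also supplies the masked analyst, so whoever prepares these tables should not be that analyst. And with 25 per arm only a large difference in infection will show, so an unremarkable first table should not be read as evidence of safety.
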